### Consent

If eligible, patients will be given verbal and written information on the study by the CI during their consultation to avoid sensitisation to the objectives of the study. One key aspect of the study is to avoid priming patients about the potential benefit of education (utilising a post-test-only design). If patients are willing to participate, written informed consent will be obtained by the CI at the same consultation. There is, therefore, a limited time frame for patients to make a decision about participation. However, the patient information sheet will stress that there is a ‘cooling-off’ period and that patients can change their mind regarding participation at any given time. If a participant is already enrolled in another study, then he/she will be allowed to participate in this trial provided the other study does not exclude him/her from doing so.

### Sample size

The anticipated patient sample size of 122 will be recruited over a 12-month period. Power calculations for sample size, 90 % power and 5 % significance, based on two-sided Mann–Whitney *U* test for the primary outcome measure, patient knowledge of glaucoma. A priori power calculations, using GPower 3.1 software, result in the following sample sizes summarized in Table 2. The calculation also takes into account a 20 % drop-out rate over the initial 9–12-month follow-up period before patients return for their regular glaucoma follow-up and knowledge questionnaire visit.

**Table 2 Tab2:** Sample size calculation

Mean score control group (± SD)	Mean score intervention group (± SD)	Required total sample size, n
7 (3)	8 (3)	400 (200 per group)
7 (3)	9 (3)	122 (61 per group)
7 (3)	10 (3)	58 (29 per group)

*SD* standard deviation

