**Methods/Design:**

HOPE Glaucoma is a 3-year, prospective, parallel-group, pragmatic, single-centred, randomised controlled trial. An anticipated 122 adults, newly diagnosed with glaucoma (including ocular hypertension, suspected glaucoma and/or chronic open-angle glaucoma) will be recruited from a nurse-led ophthalmology outpatient clinic at a medium-sized NHS Trust. Participants will be randomly allocated to receive standard clinical care (control arm) or standard care plus a glaucoma personal record, detailing the current state of their condition (interventional arm). Participant assessments are designed to test whether provision of a glaucoma personal record 1) improves patient knowledge of glaucoma and 2) contributes to improvements in clinical outcomes, i.e. delay of visual field loss. The primary outcome measure is better client knowledge of glaucoma at the 9–12 month follow-up visit. Secondary outcome measures include the rate of visual field loss and patient-reported outcome measures on visual function (National Eye Institute VFQ – 25) measured at baseline, 9–12 months, 24 months and 36 months. Estimating a 20 % drop-out rate, the study will have 90 % power to detect a mean two-point difference in glaucoma knowledge score between groups at 5 % significance - based on two-sided Mann–Whitney *U* test.

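### Table 2 handles drop-out inconsistently: the one-point row carries no allowance, and the two-point row (122) gives about 89% rather than 90% power on the stated Mann–Whitney basis

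*Protocol article*

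**What the plan says.** The Sample size section plans for "90 % power and 5 % significance", "based on two-sided Mann–Whitney *U* test for the primary outcome measure", with GPower 3.1 as the software. Table 2 takes a control mean of 7 and SD 3 in both groups and gives three totals:

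- one-point difference (7 v 8): "400 (200 per group"
- two-point difference (7 v 9): "122 (61 per group"
- three-point difference (7 v 10): "58 (29 per group"

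The two-point row is the one the trial adopted. On drop-out the section says: "The calculation also takes into account a 20 % drop-out rate over the initial 9–12-month follow-up period". The abstract (Methods/Design) repeats the claim for the adopted row: "Estimating a 20 % drop-out rate, the study will have 90 % power to detect a mean two-point difference". The article prints neither the number of completers before inflation, nor the inflation formula, nor the parent distribution used for the Mann–Whitney calculation.

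**The concern.** The rows do not scale as they should. For fixed SD, power and significance level, halving the difference should multiply the sample size by about four. From the two-point to the one-point row the printed totals rise only by 400/122 = 3.28. A single allowance applied to every row would cancel out of that ratio, so the first two rows cannot both rest on the same drop-out basis.

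Two things follow if this is right. First, a reader comparing the rows sees a one-point difference costed too cheaply. Second, the 90% power stated for 122 needs checking, because it depends on how the 20% was applied. The sample size and the power claim are published figures against which the results will be read.

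**Working it through.** **Inputs.** From the Sample size section and Table 2: two-sided 5%, power 90%, SD 3, differences 1, 2 and 3, so d = 1/3, 2/3 and 1; drop-out 20%. From Randomisation: 1:1 allocation. Assumption: normal parent, so the asymptotic relative efficiency (ARE) of Mann–Whitney to the t test is 3/π = 0.955.

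**Method.** ARE approach: with n per group, df = 2n × ARE − 2 and noncentrality = d × √(n × ARE / 2). Power comes from the noncentral t distribution. The required n is the smallest integer reaching 90%.

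**Step 1: completers per group, and what each inflation rule gives.**

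| Difference | Completers per group | × 1.2 | ÷ 0.8 | Printed per group |
|---|---|---|---|---|
| 1 | 200 | 240 | 250 | 200 |
| 2 | 51 | 61.2 | 63.75 | 61 |
| 3 | 24 | 28.8 | 30 | 29 |

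The first printed row equals the uninflated figure exactly. The second and third match the × 1.2 column to the nearest integer. Dividing by 0.8, the rule that leaves the required completers after 20% loss, gives 250, 64 and 30 per group, or 500, 128 and 60 in total.

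**Step 2: can another basis reproduce all three rows?**

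- t test: 191, 49 and 23 completers per group. Divided by 0.8: 238.75, 61.25 and 28.75. This matches 61 and 29, but not 200.
- Logistic parent: 174, 45 and 21 per group. × 1.2 gives 208.8, 54 and 25.2; ÷ 0.8 gives 217.5, 56.25 and 26.25. No row matches.

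Neither basis reproduces the table with one rule. For the normal-parent Mann–Whitney and t-test bases, an inflated first row lies between 458 and 500 in total, never 400.

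**Step 3: power of the first row after 20% loss.** 200 × 0.8 = 160 per group. With d = 1/3 and a normal parent, power is 82.7%.

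**Step 4: power of the adopted row after 20% loss.** 122 × 0.8 = 97.6, about 98 evaluable or 49 per group. With d = 2/3:

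| Basis | Power at 49 per group |
|---|---|
| Mann–Whitney, normal parent | 89.1% |
| t test | 90.4% |
| Mann–Whitney, logistic parent | 92.8% |

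At 48 per group the normal-parent figure is 88.4%. The 102 completers needed for 90% survive from 122 only if loss stays at or below 20/122 = 16.4%. Randomising 128 leaves about 102 and gives 90.3%.

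**Step 5: the third row.** 58 × 0.8 = 46.4, or 23.2 per group, where power is 90.2%; at a whole 23 per group it is 89.9%. The move from 58 to 60 is in effect a rounding matter.

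**The case against.** The strongest reply is that the adopted row is almost right. Ninety per cent is a rounded planning figure resting on an assumed SD and an assumed loss. A gap of one point, or 6 patients (128 − 122), changes no decision, and the one-point row was never the basis of the trial. All of this stands, and it is why the point is minor.

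It is also fair that 61 and 29 alone cannot show which inflation rule was used. A t-test base divided correctly by 0.8 gives the same two figures. The exact 200 in the first row, together with the Mann–Whitney test named in the text, makes the × 1.2 reading the more likely one, but does not prove it.

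Three stronger readings are tempting and not supported:

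- **That the trial is underpowered.** The shortfall is about one percentage point on one reading of an unstated option, and absent on two others.
- **That the sponsor demonstrably used the wrong inflation formula.** The article shows no formula.
- **That the shortfall should be judged under the software's most conservative (minimum-ARE) option.** That option needs 221 per group in the first row before any drop-out, so it does not fit the printed 200.

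What the reply does not remove is the first row. Whichever basis rescues 122, the printed 400 still disagrees with the statement that drop-out was taken into account.

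**Conclusion.** The concern holds as an internal inconsistency in Table 2, of minor severity. The first row has no drop-out allowance although the text says the calculation includes one: it is 100 patients short of 500, with about 83% power after 20% loss. That the rows do not share one basis follows from the printed totals alone. That the first row is the uninflated one rests on the normal-parent Mann–Whitney calculation, which reproduces 200 exactly.

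For the adopted row the stated 90% becomes about 89%, conditional on a normal parent, SD 3 and a full 20% loss. The × 1.2 explanation is an inference. Nothing here calls the planned 122 into question.

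**What to change.** Keep 122. Restate the power in the abstract and the Sample size section along these lines: *122 randomised, about 98 evaluable after 20% loss, giving about 89% power for a two-point difference (SD 3, two-sided 5% Mann–Whitney, normal parent).*

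Put Table 2 on one drop-out basis: 500 (250 per group), 128 (64) and 60 (30). Add a column with the completers needed (200, 51 and 24 per group) and give the inflation formula, n / (1 − 0.2). Add a note that 122, not 128, is the adopted target, with the power just stated. If the calculation in fact rested on a t test or another parent distribution, say so and recompute all three rows on that basis.

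The cost is a text correction. It needs no extra patients and no change in conduct; the stated power becomes about one percentage point less favourable.

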### Randomisation

Each participant will be assigned to the control or interventional arm by a pragmatic randomisation approach; there will be no stratification and randomisation will take place on a 1:1 ratio without blocking. Online freeware will be used to generate a random allocation sequence in advance of the recruitment period, seen only by the trial administrator (who will not be involved with data collection) [9]. Allocation concealment will be achieved using consecutively numbered, sealed, opaque envelopes prepared in advance of recruitment by the trial administrator. This will ensure the investigator is not aware of the allocation sequence in advance of randomization. Eligible subjects will be randomised and - if assigned to the intervention arm - presented with their glaucoma personal record by the CI immediately after written informed consent has been obtained. For overview of the study process, see Fig. 1.

**Fig. 1 Fig1:**
[figure not shown]
HOPE trial schema

### Intervention description

Both groups will have exposure to current educational resources and materials presented at diagnosis, as is standard clinical practice. This may include an enlarged model of the eye, ocular anatomy posters, ocular coherence tomography sample scans, images of healthy and damaged optic nerve heads, examples of normal visual field tests and those showing glaucomatous loss, and a glaucoma information leaflet to take away with them. The chief investigator’s contact number will also be provided, as would be standard in her capacity as clinical nurse specialist in ophthalmology.

Those participants allocated to the interventional arm will, in addition to standard clinical care, be provided with their own ‘glaucoma personal record’ (Additional file 1), which will be personalised to document the current state of each participants’ glaucoma diagnosis and utilised during ophthalmologic review. Both groups of participants will be asked to complete the National Eye Institute Visual Functioning Questionnaire – 25 (VFQ-25) to gain an insight into patients’ perceptions about the impact that glaucoma may have on their daily living. The ‘glaucoma personal record’ will be administered to those participants randomised to receive the intervention by the CI immediately after the informed consent process has been completed.

### Intervention development

Recent work by Waterman [10] identified the need for patients to be informed about their glaucoma, to help them understand their condition and the implications of poor medication adherence. The glaucoma personal record used in the HOPE Glaucoma trial (Additional file 1) was developed from the concept of the Spaeth-coloured glaucoma graph for diagnosed glaucoma patients and glaucoma suspects [11]. This graph provides both patients and clinicians with visual information concerning current optic disc appearance. Spaeth and Paulus [11] claimed it is user-friendly because of the traffic light system. They also claimed that most patients understand that green indicates ‘safe’, yellow/amber means ‘caution’, and red means ‘danger’. They proposed that “the graph can help in patient counselling by increasing the understanding regarding the disease status”. The work from Spaeth and Paulus inspired application of a traffic light system to visual field scoring using the Hoddap Classification [12, 13].

Although staging systems may be of limited value in clinical practice, the authors intended to put together an inexpensive yet useful ‘glaucoma personal record’. The Hoddap system has three stages, namely, early, moderate and advanced glaucomatous loss. The rate of progression of visual field loss will be measured by regression analysis of the mean deviation from the mean, expressed in decibels per year. Since this glaucoma personal record is intended to help patients understand their current measures according to a traffic light system, best evidence available has to be balanced with simplicity, in order to be useful.

The third fundamental measure obtained at regular glaucoma review appointments is intraocular pressure (IOP). Elevated IOP above 21 mmHg is considered a major risk factor in glaucoma pathology. Normal IOP is considered to be less than or equal to 20 mmHg. Applying the traffic light system here means lower IOPs lie within the green ‘safe’ zone. IOPs between 21 and 30 mmHg - the amber zone - are observed with caution, although many other factors must be taken into consideration e.g. central corneal thickness, visual field loss or suspicious optic discs. Any IOP above 30 mmHg, the red zone, usually means antihypertensive treatment is required as risk of glaucomatous damage or vein occlusion is considered too high to leave untreated.

The current glaucoma personal record under investigation is a coloured, A5-sized (or A4 if required), booklet of 16 pages. It was refined with advice from the International Glaucoma Association, who provided financial sponsorship for this study. This prototype glaucoma personal record is open to development and further refinement, depending on feedback and outcomes of this study.

### Objective

This study aims to assess whether patient education, through the provision of a glaucoma personal record, results in increased knowledge of their condition and whether this contributes to positive behavioural change and a reduction in the rate of visual field loss. The null hypothesis is that a patient-specific glaucoma personal record has no effect on client knowledge of glaucoma (OHT, SG or CAOG), quantified using a validated researcher-conducted survey at 9–12 months post-recruitment.

### Outcome measures

#### Primary outcome

The primary outcome measure is client knowledge of glaucoma, quantified using a validated researcher-conducted survey at 6–12 months post-recruitment [8], see Table 3. This survey and scoring system was used, and validated by ophthalmic colleagues in 2009/2010 “to establish the impact of educational support on clients’ knowledge of glaucoma and adherence, in preparation for a further interventional study” [9]. It provides an ordinal score of participants’ knowledge. The primary outcome measure is therefore the degree of understanding and knowledge retention of their OHT, SG, or COAG in the interventional group compared with the control group. Patients requiring ocular antihypertensive treatment at first presentation are eligible for inclusion in this trial; the total knowledge score achievable is either 12 for those not prescribed antihypertensive drops, or 17 for those prescribed eye drops during the course of the study. The survey will be administered by the CI when participants attend a ‘glaucoma review’ outpatient clinic between 6 and 12 months post-recruitment.

**Table 4 Tab3:** Overview of study timeline and outcome measures

Baseline	Baseline	9–12 months	24 months	36 months
Patient knowledge		X		
Patient perspective (VFQ-25)	X	X	X	X
Clinical parameters	X	X	X	X

*VFQ-25* National Eye Institute Visual Functioning Questionnaire – 25

#### Secondary outcomes

The secondary, longer-term, outcome measure is rate of visual field loss. In line with clinical practice, visual field loss will be measured at least annually (more frequently if there is a clinical indication). The relative visual loss rates between control and intervention groups will also be measured annually. Visual field testing will be performed by standard automated perimetry (SAP) using the Humphrey Central 24–2 programme. The Humphrey perimeter provides print-outs with statistical analyses of single field-test results, including numerical indices of reliability, and deviation from the norm of age-matched visual field analyses. The visual field indices used to identify progression of visual field loss will be mean deviation (MD) from the mean. MD represents the average difference between normal age-corrected sensitivity values and the subjects’ measured values at all test points. The rate of progression of visual field loss will be measured by linear regression analysis of the MD from the mean, expressed in decibels per year (or the newer visual field index, which was not available at the start of this study).

A simple measure was selected for use in this trial. However, there are challenges to using visual field analyses to detect progression. The test is subject to variability in performance, even for the same patient. Modern perimetry attempts to reduce sources of error in, for example, reduced test time, continuous gaze/fixation monitoring. The role of the operator is crucial in assisting patients to perform the test as accurately as possible [13]. All visual field testing will be undertaken by the CI to reduce inter-assessor variability.

Trend analyses to quantify rate of visual field loss require at least five tests to detect progression. This means relatively frequent testing in the first 2 years following diagnosis, especially if patients initially present with loss. The European Glaucoma Society (EGS) suggest three tests a year in the first 2 years. As such, this secondary outcome measure will take approximately 2–5 years to establish. The MD score will be documented in the ‘glaucoma personal record’ for the intervention group, and obtained from standard medical records for the control group.

The impact of visual field loss on patients’ lives will be measured using the vision-targeted health-related quality of life (HRQOL) measure: the National Eye Institute Visual Functioning Questionnaire – 25 (VFQ-25). This validated patient-reported outcome measure tool was designed to measure the impact of visual deficit on physical functioning, emotional well-being and social functioning [14]. The VFQ-25 will be completed by participants attending the CI’s nurse-led glaucoma review outpatient clinic at baseline, 6–12 months, 24 month and 36 months post-recruitment.

The patient glaucoma record will use ‘traffic light’ graphs to make it more straightforward for patients to see the status of their glaucoma for e.g. visual field loss [11]. A copy of the patient glaucoma record is available (Additional file 1).

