### Data collection and monitoring

Participant follow-up will be 3 years. The estimated primary completion date is September 2015 and the estimated study completion date is September 2017. An overview of the study timeline and recorded outcome measures are detailed in Table 4. Outcome data will be collected during clinically scheduled ophthalmology outpatient appointments with the CI and subjects will not be asked to attend any additional clinic appointments above those required for their clinical care. This design was used to increase the pragmatism of the study and improve subject retention throughout the duration of the study. Outcome data will not be collected for patients that withdraw from the study or deviate from the study timeline.

**Table 3 Tab4:** The scoring system used to establish participants’ knowledge of glaucoma and its management. Source: [9]

Number	Question	Scored 0	Scored 1	Scored 2	Scored 3	Max score
1	Can you tell me what you think glaucoma is?	Don’t know/ incorrect answer	Build up of pressure, raised/high pressure, nerve damage, loss of vision	Optic nerve damage, irreversible vision loss, chronic disease, slowly progressive (in own words)	NA	2
2	Can you tell me which part of the eye can become damaged with glaucoma?	Don’t know/ incorrect answer	Back of the eye	Retina	Optic nerve	3
3	Can you tell me what effect glaucoma has on vision if left untreated?	Don’t know/ incorrect answer	You go blind/you gradually go blind/ you lose vision	You get tunnel vision	NA	2
4	Can you tell me what part of vision glaucoma affects the most?	Don’t know/ incorrect answer	Visual field/field of vision/side vision	NA	NA	1
5	Is glaucoma hereditary/does glaucoma run in families?	No/don’t know	Yes	NA	NA	1
6	Do you know what investigations/tests will be carried out regularly at future clinic appointments to monitor changes in your eyes?	Don’t know/ incorrect answer	Either IOP measurement, visual field test or optic nerve examination (in own words)	Any two of the tests (in own words)	All three tests (in own words)	3
7	Do you know the name(s) of the drop(s) that has/have been prescribed for you?	Don’t know/ incorrect answer	Yes (client named the drops)	NA	NA	1
8	Do you know what the drops do?	Don’t know/ incorrect answer	Lower/reduce/control eye pressure	NA	NA	1
9	Do you know when you will need to collect your next prescription?	Don’t know/ incorrect answer	1 month/28 days	NA	NA	1

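### The visual field outcome is defined as a regression slope with a five-test minimum, but the schedule guarantees four tests and the stated analysis uses two

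*Protocol article*

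**What the plan says.** All places are in the protocol article.

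- **Outcome definition (Secondary outcomes).** Rate of visual field loss is the linear-regression slope of MD, in dB per year. On what such an analysis needs: "Trend analyses to quantify rate of visual field loss require at least five tests to detect progression". The section infers fairly frequent testing in the early years, above all for patients who present with loss, and cites a guideline: "The European Glaucoma Society (EGS) suggest three tests a year in the first 2 years". It concludes that "this secondary outcome measure will take approximately 2–5 years to establish".
- **Testing commitment (same section).** "visual field loss will be measured at least annually (more frequently if there is a clinical indication". Loss rates in the two arms are also to be compared every year.
- **Schedule.** The study timeline table has the row "Clinical parameters X X X X", with columns for baseline, 9–12, 24 and 36 months. The abstract says the secondary outcomes are "measured at baseline, 9–12 months, 24 months and 36 months". Under Data collection and monitoring, "Participant follow-up will be 3 years" and "subjects will not be asked to attend any additional clinic appointments above those required for their clinical care".
- **Analysis (Data analysis).** Average field measurements at baseline and at 36 months are compared within each arm by a paired test and between arms by a t test or Mann–Whitney U test. No slope enters this analysis.
- **Role in the trial.** The abstract and the Objective both present slower field loss as something the trial is meant to assess. The sample size section covers the knowledge score only.

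**The concern.** One outcome carries three different data requirements: five tests in the definition, four in the guaranteed schedule and two in the analysis. Someone analysing the trial from this text has to choose among them after the data are in.

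The choice matters most if the five-test minimum is taken as a condition for analysis. A participant seen only at the scheduled visits has four fields and would drop out. Those who remain would be the ones tested more often for a clinical reason that arose after randomisation. The chief investigator does all the field testing, provides the care and knows the allocation (Secondary outcomes; Discussion), so reaching five tests could depend on both suspected worsening and arm. The comparison would then no longer be between the groups as randomised.

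If the minimum is ignored without comment, the report would rest a statement about progression on fewer tests than the protocol says are needed. A null result at 36 months could also be read as showing that the record does not slow field loss, although the trial was not sized for that question.

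**Working it through.** **1. Count of tests.** The plan's own figure here is the minimum of five.

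- Guaranteed by month 36: baseline + 9–12 + 24 + 36 months = 4. Shortfall: 5 − 4 = 1.
- With annual testing only, the fifth field falls at month 48, which is 48 − 36 = 12 months after follow-up ends.
- The cited guideline pattern would give 3 × 2 = 6 tests by month 24, and 7 with the month-36 test. It is cited, not adopted as the trial schedule.
- The stated horizon of 2–5 years extends up to 2 years beyond the 3-year follow-up.
- Data analysis uses 2 tests per participant.

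**2. Inputs for precision.** The article gives no variability for MD, so these are assumptions: residual (test-retest) SD σ = 1 dB, range 0.5–2 for one patient and 1–2 for the arms; SD of true slopes between patients τ = 0.5 dB/year, range 0.3–1.0. Participants per arm: 61 × 0.8 = 48.8, taken as 49. The 20% drop-out in the sample size section covers only the initial 9–12 months, so 49 at 36 months is optimistic.

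**3. One patient's slope.** With test times t, S = Σ(t − mean t)², SE = σ/√S, and the 95% half-width is t(0.975, k − 2) × SE for k tests.

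- Four tests at 0, 1, 2, 3 years: S = 5.0, SE = 0.447σ, half-width 4.303 × 0.447 = 1.92 dB/year at σ = 1 (0.96–3.85). With the follow-up visit at 10.5 months instead of 12, S = 5.14 and the half-width is 1.90.
- Five tests at 0, 0.5, 1, 2, 3 years: S = 5.8, half-width 3.182 × 0.415 = 1.32 (0.66–2.64).
- Seven tests (guideline pattern plus month 36): S = 6.23, half-width 2.571 × 0.401 = 1.03 (0.51–2.06).

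Four tests give an estimable slope with 2 residual degrees of freedom, but a very imprecise one for an individual.

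**4. Between-arm difference in mean slope.** SE = √[(2/49)(τ² + σ²/S)]. The difference detectable with 80% power at two-sided 5% is 2.80 × SE. For four tests: √[(2/49)(0.25 + 0.20)] = 0.1355, and 2.80 × 0.1355 = 0.38 dB/year.

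| Tests used | S | Detectable difference, σ = 1, τ = 0.5 | Range (σ 1–2, τ 0.3–1.0) |
|---|---|---|---|
| 2 (0 and 3 years) | 4.5 | 0.39 | 0.32–0.78 |
| 4 | 5.0 | 0.38 | 0.30–0.76 |
| 5 | 5.8 | 0.37 | 0.29–0.74 |
| 7 | 6.23 | 0.36 | 0.28–0.73 |

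The number of tests matters a good deal for an individual and very little for the arms. The comparison between arms is limited by the number of participants and by true variation between them.

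**The case against.** A reader might infer that the four-visit schedule makes the test of delayed field loss impossible to deliver, whichever between-arm test is used. The documents do not support that, for four reasons.

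- Four is a floor. Testing is at least annual, the section expects more frequent testing early on, all participants are newly diagnosed, and the timeline row does not cap the number of fields. Some participants may well reach five.
- The five-test sentence concerns detecting progression by trend analysis. The comparison in Data analysis uses no trend and needs two fields, which the schedule supplies.
- A comparison of mean slopes is also computable from four tests, and a fifth changes the detectable difference by only about 0.01 dB/year.
- Nowhere does the article say that participants with fewer than five fields are left out. The selection problem is a risk left open, not a planned analysis.

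It can be added that the outcome is labelled secondary and longer-term, that the section itself warns about the variability of field tests, and that the null hypothesis concerns knowledge alone.

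All of this stands, and it limits the point. It does not remove the mismatch. Extra tests on clinical indication are not guaranteed to anyone. The two-time-point test answers a different question from the slope named as the outcome. The article does not say what the five-test minimum is for. A separate analysis plan might add detail, but this article states its analysis explicitly, and that analysis conflicts with its own definition.

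**Conclusion.** The point holds as an inconsistency between definition (five tests), guaranteed schedule (four) and analysis (two). The count rests on the text alone.

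For participants tested only at the scheduled visits, the protocol's own criterion for detecting progression is missed by one test. At an assumed residual SD of 1 dB, one such patient's slope is known only to within about ±1.9 dB/year (0.96–3.85 over SDs of 0.5–2 dB). Applying the minimum as a filter would select participants after randomisation.

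The comparison between arms survives. The detectable difference is about 0.38 dB/year (0.30–0.76 over the assumed ranges), and no power calculation in the article covers it. These figures depend on assumed SDs and on 49 participants per arm at 36 months, which is optimistic. They do not show that the schedule is what limits the between-arm comparison.

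**What to change.** Reconcile the timeline table, Secondary outcomes and Data analysis:

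1. In Data analysis, replace the two-time-point tests of visual field loss with the between-arm difference in mean MD rate (dB/year) and its 95% confidence interval. Use all available fields from every randomised participant, for example in a mixed model with time, arm and time by arm.
2. In Secondary outcomes, state that the five-test minimum concerns progression in an individual and is not used to select participants. Say that the number of fields may differ between participants because extra tests follow clinical indication. A sensitivity analysis restricted to fields from the scheduled visits would show whether this matters.
3. In the abstract, the Objective and Secondary outcomes, state that the field comparison is unpowered, that the guaranteed schedule does not establish progression in individuals, and that a null result at 36 months is not evidence of no effect.

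Cost: changes of wording, slightly more analysis work, and a less favourable claim of clinical benefit. No visits or tests are added, and clinical testing frequency is left as it is.
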